## Abstract

**Background:**

After liver resection (LR), patients with hepatocellular cancer (HCC) are at high risk of recurrence. There are no approved anti-cancer therapies known to affect such risk, highlighting the acute need for novel systemic therapies to control the probability of disease relapse. Immunotherapy is expanding as a novel treatment option for HCC. Emerging data from cohort 4 of the CA209–040 study, which investigated the safety and preliminary efficacy of nivolumab/ipilimumab co-administration in advanced HCC, suggest that the combination can be delivered safely with an acceptable proportion of reversible grade 3–4 toxicities (27.1%) and a low discontinuation rate (2%) in patients with HCC. Here, we describe the design and rationale of PRIME-HCC, a two-part, multi-centre, phase Ib study to assess safety and bioactivity of the nivolumab/ipilimumab combination prior to LR in early-stage HCC.

**Methods:**

The study involves an initial safety run-in phase (Part 1) to allow for preliminary safety characterisation within the first 6 patients enrolled and a subsequent expansion (Part 2). Ipilimumab will be administered once only on Day 1. Nivolumab will be administered on Day 1 and Day 22 (± 3 days) for a total of two 21-day cycles (i.e. 6 weeks of treatment). The primary objective of the study is to determine the safety and tolerability of the nivolumab/ipilimumab combination prior to LR. The secondary objective is to preliminarily characterize the efficacy of the combination prior to LR, including objective response rate (ORR) and pathologic response rates. Additional exploratory objectives include preliminary evidence of long-term disease control and to identify predictive correlates of response to the nivolumab/ipilimumab combination in HCC.

**Discussion:**

The results of this study will help define the positioning of neoadjuvant nivolumab/ipilimumab combination in the perioperative management of HCC, with potential to improve survival outcomes in this patient population.

**Trial registration:**

EudraCT Number: 2018–000987-27 Clinical trial registry & ID: ClinicalTrials.gov: NCT03682276.

**Supplementary Information:**

The online version contains supplementary material available at 10.1186/s12885-021-08033-x.

## Background

Hepatocellular carcinoma (HCC) is the sixth commonest and third most lethal solid malignancy on a global scale [1]. In spite of the major diagnostic advancements, only one out of three of the newly diagnosed patients are eligible for radical treatments upfront [2]. In patients within the Barcelona Clinic Liver Cancer (BCLC) stage 0 or A criteria, surgical resection can be carried out safely with curative intent [3]. However, this is only feasible in < 30% of the patients, mainly due to the extent of radiological spread of the disease or poor synthetic function due to underlying cirrhosis.

### The evolving landscape of systemic therapy for HCC

Anti-tumour immunotherapy with monoclonal antibodies blocking the programmed death-1/programmed death-ligand 1 (PD-1/PD-L1) and cytotoxic T-lymphocyte-associated protein 4 (CTLA-4) pathways are gaining momentum, where immune checkpoint inhibitors directed against these targets either alone or in combination have shown efficacy in HCC. Pembrolizumab has shown initial evidence of disease-modulating activity in a little less than 20% of patients enrolled in Keynote-224 [4], but failed to improve OS in Keynote-240, a placebo-controlled phase III trial which investigated pembrolizumab in treatment-experienced patients with advanced HCC [5]. CheckMate-040 (CA209–040) is the reference, open label, multi-cohort, phase I/II study which evaluated safety and efficacy of nivolumab in advanced HCC patients [6]. Despite evidence of anti-tumour activity, the subsequent phase III study CheckMate-459 failed to confirm thedif significant superiority of first-line nivolumab over sorafenib with respect of OS in the advanced disease (HR = 0.85, 95% CI: 0.72–1.02; *p* = 0.0752) [7].

Whilst not yet supported by evidence of OS improvement, dual CTLA-4/PD-1 blockade might also be beneficial, given the different and alternative role of the two biologic axes within the cancer immunity cycle, as CTLA-4 is a key driver in downregulation of tumour-antigen presenting cells and in T-regs enhancement, whereas PD-1/PD-L1 mainly impairs the efficiency of the CD8 + CTL response. Reliable evidence of synergistic effects from CTLA-4/PD-1 co-inhibition has been observed in clinical trials amongst other tumour types, in melanoma [8], renal cell carcinoma [9] and NSCLC [10].

In HCC, safety and preliminary efficacy of 3 alternative schedules of nivolumab and ipilimumab have been investigated within the cohort 4 of Checkmate-040. Pre-treated patients with Child-Pugh class A advanced disease have been randomised to receive either nivolumab 3 mg/kg + ipilimumab 1 mg/kg or nivolumab 1 mg/kg + ipilimumab 3 mg/kg or every 3 weeks for four doses followed by maintenance nivolumab monotherapy (240 mg flat dose biweekly) until disease progression or unacceptable toxicity. The further arm evaluated nivolumab 3 mg/kg + ipilimumab 1 mg/kg every 6 weeks until unacceptable toxicity or disease progression. The incidence of treatment related adverse events (TRAEs) for the whole cohort was 37% with a 5% discontinuation rate. The efficacy analysis showed the nivolumab/ipilimumab combination to achieve an ORR of 31%, which was higher than the ORR (14%) reported with single agent nivolumab in the same study, and led to US Food and Drug Administration approval of the nivolumab/ipilimumab combination in treatment-experienced advanced HCC patients [11].

### Neoadjuvant immunotherapy

The rapidly changing landscape of systemic therapy in HCC, where combination immunotherapy has led to reproducible evidence of disease-modulation, has prompted clinicians to consider the expansion of immunotherapy to the earlier stages of the disease. There is an acute need for highly active systemic anti-cancer treatments as a pre-operative strategy to attempt disease down-staging and expand the proportion of patients who might benefit from curative surgery. Furthermore, despite optimal local control of the disease, the majority of patients recur within 2 years of surgery as a likely result of proliferation of microscopic neoplastic foci within the residual organ, and the 5-year survival rate for early-stage HCC ranges between 17 to 53%, with a recurrence rat that can reach 70% also in the curative resection setting [2, 12]. The negative impact on survival secondary to both early and late recurrence of HCC suggests the need for an optimal integration of systemic anti-cancer therapies to control the risk of relapse and increase the chances of cure in patients with early stage HCC.

Currently, there is no standard of care for adjuvant/neoadjuvant treatment and although a number of approaches have been attempted including trans-arterial chemoembolization (TACE), Yttrium-90 radioembolization, and neoadjuvant sorafenib in HCC patients on waiting list for liver transplantation [13–15]. Failure to control micro-metastatic disease is a major determinant influencing early relapse and mortality following curative resection and randomized controlled trials have shown sorafenib, to be ineffective in improving outcomes in the adjuvant setting [16].

Here, we describe the design and the rationale of PRIME-HCC, a two-part multi-centre phase Ib study to assess safety and bioactivity of the nivolumab and ipilimumab combination before LR in patients with HCC.

## Methods/design

PRIME HCC is a two-part, phase Ib study of ipilimumab and nivolumab combination prior to LR in adult patients (aged ≥18 years) with HCC. Ipilimumab will be administered once only on Day 1. Nivolumab will be administered on Day 1 and Day 22 (± 3 days) for a total of two 21-day cycles (i.e. 6 weeks of treatment). Part 1 of the study will initially consist of a safety run-in phase of 6 participants. If two or fewer surgical delays are observed, the study will continue to Part 2, which will consist of an expansion phase including up to 26 participants. All participants entered into the study will receive nivolumab and ipilimumab for a fixed duration of 6 weeks of treatment. The study flow-chart is summarized in Fig. 1**.**

**Fig. 1 Fig1:**
[figure not shown]
PRIME-HCC study objectives and timeline (original figure, no copyright permission required; Created with BioRender.com)

Ipilimumab is a fully human monoclonal immunoglobulin (Ig) G1k specific for human CTLA-4 manufactured by Bristol Myers Squibb (BMS). Nivolumab is a human monoclonal antibody (HuMAb; immunoglobulin G4 [IgG4]-S228P) manufactured by BMS that inhibits the PD-1 receptor on cell surface. The clinical safety profile of nivolumab and ipilimumab as a combination therapy has emerged from a number of clinical studies in a number of tumour types [17–22].

In PRIME-HCC the dosing schedule adopted is 1 mg/kg dose Q6W for ipilimumab in combination with nivolumab 3 mg/kg Q3W for a total of 2 cycles. The rationale for dose selection stems from the clinical experience in the use of the combination across a number of indications. In the specific setting of HCC, whilst there is currently no clinical data available to illustrate the safety and tolerability of the planned regimen administered sequentially with LR, similar dosing schedules including a six-weekly dosing of ipilimumab at 1 mg/kg and three-weekly dosing of nivolumab at 3 mg/kg have been explored in CA209–040 cohort 4. Extrapolating from CA209–040 safety data, ipilimumab dose intensity appears to be the strongest determinant of toxicity, in particular with regards to immune-related liver TRAEs: study treatment in Arms B and C, where ipilimumab dose intensitiy was lower, was shown to be better tolerable compared to more intense ipilimumab dosing schedules (3 mg/kg in Arm A). For this reason, PRIME-HCC will utilise the lowest effective dose intensity schedule (1 mg/kg Q6W) and combine it with nivolumab at the clinically approved dose of 3 mg/kg Q3W. The choice of this combination will maintain individual exposures that are optimally consistent with those associated with maximal efficacy response in other indications and that are tolerated and safe, especially considering liver-related TRAEs in a patient population where cirrhosis and concomitant chronic viral infection is highly prevalent.

### Eligibility criteria

Detailed eligibility criteria are provided in Table 1**.** In brief, PRIME-HCC will recruit patients amenable to resection and ineligible for liver transplantation, with a confirmed diagnosis of HCC by biopsy or by non-invasive diagnostic criteria of the American Association for the Study of the Liver (AASLD).

**Table 1 Tab1:** Eligibility criteria of PRIME-HCC trial

Key inclusion criteria	Key exclusion criteria
1. Written informed consent for the trial 2. Aged ≥18 years 3. Confirmed diagnosis of HCC 4. Willing to provide tissue from an excisional biopsy of a tumour lesion 5. Have measurable disease by CT-scan or MRI defined by RECIST 1.1 criteria 6. Ineligible for liver transplantation 7. Medically fit to undergo surgery as determined by the treating medical and surgical oncology team. 8. ECOG-PS 0 or 1 9. Adequate hematologic function, defined as WBC ≥ 2000/μl, ANC ≥ 1500/μl, platelet count ≥50,000/μl and hemoglobin ≥8.5 g/dl without transfusion or Erythropoietin dependency. 10. Adequate renal function, defined as creatinine ≤1.5× ULN or measured or calculated creatinine clearance ≥40 ml/min for those with creatinine levels > 1.5× ULN 11. Adequate hepatic function, defined as total bilirubin ≤1.5× ULN, and ALT/AST levels ≤5× ULN, albumin ≥2.8 g/dL 12. Adequate coagulation function, defined as INR ≤ 1.5× ULN unless the patient is receiving anticoagulant therapy as long as PT or aPTT is within the therapeutic range 10. Overall Child-Pugh class A 11. Female patient of childbearing potential should have a negative serum pregnancy test within 24 h of her first dose of IMP 12. Women of childbearing potential must be willing to use a highly effective method of contraception 13. Sexually active males must agree to use an adequate method of contraception	1. Extrahepatic metastasis 2. Prior systemic anticancer treatment for HCC, including an anti-PD-1, anti-PD-L1 or anti-CTLA-4 antibody 3. Prior orthotopic liver transplantation 4. Any major surgery within the 3 weeks prior to enrolment 5. Hepatic encephalopathy 6. Ascites that is refractory to diuretic therapy 7. Is currently receiving anti-cancer therapy (chemotherapy, radiation therapy, immunotherapy or biologic therapy) or has participated or is participating in a study with Nivolumab or Ipilimumab or used an investigational device within 4 weeks of the first dose of IMP 8. Diagnosis of immunodeficiency or is receiving systemic steroid therapy or any other form of immunosuppressive therapy 9. Known history of active Bacillus Tuberculosis 10. History of known hypersensitivity to any monoclonal antibody or any of their excipients 11. Known additional malignancy that is progressing or requires active treatment ^a^ 12. Active autoimmune disease that has required systemic treatment in the past 2 years ^b^ 13. Known history of, or any evidence of active, non-infectious pneumonitis 14. Active infection requiring systemic therapy ^c^ 15. History or current evidence of any condition, therapy, or laboratory abnormality that might confound the results of the trial 16. Known psychiatric or substance abuse disorders that would interfere with cooperation with the requirements of the trial 17. Pregnant or breastfeeding 18. Known history of Human Immunodeficiency Virus (HIV; HIV 1/2 antibodies) 19. Received a live vaccine within 30 days of first dose of IMP

*CT* Computed tomography; *MRI* Magnetic resonance imaging; *ECOG-PS* Eastern cooperative oncology group-performance status; *WBC* White blood cells; *ANC* Absolute neutrophil count; *ULN* Upper limit of normal; *ALT/AST* Alanine/aspartate aminotransferase; *IMP* Investigational medicinal product; *PTT/PT* Partial thromboplastin time/prombin time; ^a^ Exceptions include basal cell carcinoma of the skin or squamous cell carcinoma of the skin that has undergone potentially curative therapy, or in situ cervical cancer; ^b^replacement therapy (eg. thyroxine, insulin, or physiologic corticosteroid replacement therapy for adrenal or pituitary insufficiency, etc.) is not considered a form of systemic treatment; ^c^ with the exceptions relating to Hepatitis B and C virus

Participants will require a full hepatitis serology screen prior to enrolment into the study, this includes Hepatitis B and Hepatitis C Virus serology. In patients with positive serology for either virus, baseline HBV DNA and HCV quantitative RNA levels will be requested. Participants who are confirmed to have chronic and active hepatitis B and/or C (i.e. with detectable HBV DNA or HCV RNA at baseline) will have their viral load (HCV RNA and/or HBV DNA as appropriate) monitored at each cycle and at the end of treatment follow-up visit.

### Planned sample size and study period

We designed the study as a safety-oriented trial and considered enrolling a cohort of up to 32 participants to:
Comprehensively characterise the safety profile of nivolumab and ipilimumab co-administration in patients with early-stage HCC;Preliminarily document the efficacy of treatment to inform subsequent efficacy-testing in a future adequately powered trial;Obtain adequate information regarding the disease-modulating effects from treatment reflected by the proposed exploratory endpoints.

With the primary endpoint being safety, no power calculation for hypothesis testing is required to formally power the study: the upper 95% confidence interval for toxicity events will inform the decision to proceed to a future, adequately powered, phase II trial. Part 1 of the study will initially require a total of 6 patients. If ≤2 surgical. Delays are observed (primary safety endpoint), the study will continue to Part 2 following Independent Safety Data Monitoring Committee review of preliminary safety data. A second interim analysis will be performed when 100% of the recruited patients have completed study follow-up visit 2 (FU2) to evaluate general safety and tolerability of the combination.

### Study procedures

Patients will undergo baseline tumour imaging including computed tomography (CT) scan of the chest, abdomen and pelvis, and by contrast enhanced magnetic resonance imaging (MRI) scan of the liver at screening. At post-treatment time-points prior to surgery (on Day 43), after surgery (on Day 127) and 4-monthly thereafter, tumour imaging will be repeated using contrast enhanced MRI. A triple-phase CT of the liver is an acceptable alternative for intrahepatic staging in patients with contraindications to MRI. Baseline CT/MRI scans do not need to be repeated if obtained within 35 days of first dose. The same method used for assessment at baseline must then be used at all subsequent time points. RECIST v1.1 criteria will be used to determine patient response to treatment, progression-free survival (PFS) and ORR. A baseline core tumor biopsy will be collected from participants at screening and patients will have a parcel of leftover tissue from their LR specimen stored for correlative studies. Treatment will consist of a maximum of 2 cycles of nivolumab 3 mg/kg and 1 cycle of ipilimumab 1 mg/kg administered intravenously Q3W. Patients will be reviewed following completion of IMP treatment (Follow-up visit 1; FU1) on Day 43 +/− 3, prior to surgery. LR will be performed as per standard of care. The safety FU2 will be conducted 126 days (± 7 days) after the first dose of the investigational medicinal product (IMP). All AEs that occur prior to the visit will be recorded. Participants with on-going AEs at the visit will be followed up by principal investigator (PI) or delegate until resolution or stabilisation of the event. Following FU2, participants will be assessed every 4 months (± 7 days) thereafter to collect information regarding disease status and survival. Long-term follow-up will continue, for each patient, for a total of 2 years. The Standard Protocol Items: Recommendations for Interventional Trials (SPIRIT) schedule of enrolment, interventions, and assessments is provided in Supplementary Table 1**.**

### Outcome measures and endpoints

Primary study endpoints include rate of patients experiencing a surgery delay to Day 89 or later and determination of safety and tolerability of the nivolumab/ipilimumab combination based on National Cancer Institute Common Terminology Criteria for Adverse Events (NCI CTCAE) v5.0 criteria from nivolumab and ipilimumab initiation to 126 days later.

Secondary endpoints include ORR on pre-resection imaging at day 42 according to the RECIST v1.1 criteria and pathologic response rate on evaluation of the resected specimen. Exploratory endpoints are PFS rate and OS at day 126 and every 4 months thereafter and identity of biomarkers of response to nivolumab and ipilimumab using high-throughput technologies.

### Adverse events management and dose modifications

Adverse events (both non-serious and serious) of unknown aetiology, associated with IMP exposure and likely to have an immune-mediated underlying mechanism may be considered as irAEs. These AEs may occur from soon after the first dose to months after the last dose. If an irAE is suspected, efforts will be put in place to exclude any other etiologic causes prior to labelling an AE as an irAEs. Summaries of recommendations to managing irAEs and of the physician’s guidelines for IMP’s temporary interruption and permanent discontinuation in case of toxicities are provided in Table 2 and Table 3**,** respectively**.** Treatment discontinuation for AST, ALT deterioration in participants who present with Grade 2 AST or ALT at Cycle 1 Day 1 will be triggered only if ALT or AST increase by more than or equal to 50% compared to the measurement taken at initiation of systemic treatment (Cycle 1 Day 1) and lasts for at least 1 week. In addition to the guidelines, dosing should be permanently discontinued in any participant who does not receive the Cycle 2 dose within the allowed window (Day 18 to Day 24) due to being unfit for dosing for any reason.

**Table 2 Tab2:** Summary of recommendations to managing immune-related adverse events. IrAEs: immune-related adverse events; IMP: investigational medicinal product

irAE	Supportive Care Intervention
Grade 1	Provide symptomatic treatment
Grade 2	Consider systemic corticosteroids in addition to appropriate symptomatic treatment. Steroid taper should be considered once symptoms improve to Grade 1 or less and tapered over at least 4 weeks.
Grade 3 and Grade 4	Systemic corticosteroids are indicated in addition to appropriate symptomatic treatment. May utilize 1 to 2 mg/kg prednisone or equivalent per day. Steroid taper should be considered once symptoms improve to Grade 1 or less and tapered over at least 4 weeks. Consider referral to organ-specific specialist (i.e. gastroenterologist, hepatologist, respiratory physician, endocrinologist) for any grade 3–4 irAEs, in order to evaluate substitution treatments and immune-modulating agents, such as anti-TNFα of other immune suppressants.

**Table 3 Tab3:** Summary of the physicians’ guidelines for IMP’s temporary interruption and permanent discontinuation in case of immune-related adverse events. PI: principal Investigator

Toxicity	Hold treatment for grade	Timing for restarting treatment
Diarrhoea/ Colitis	2–3	Toxicity resolves to Grade 0–1
	4	Permanently discontinue
AST, ALT, or Increased Bilirubin	2	Toxicity resolves to Grade 0–1
	3–4	Permanently discontinue (see exception below)^a^
Type 1 diabetes mellitus (if new onset) or Hyperglycaemia	T1DM or 3–4	Hold the IMP for new onset Type 1 diabetes mellitus or Grade 3–4 hyperglycemia associated with evidence of beta cell failure
Hypophysitis	2–4	Toxicity resolves to Grade 0–1. Therapy with IMP can be continued while endocrine replacement therapy is instituted
Hyperthyroidism	3	Toxicity resolves to Grade 0–1
	4	Permanently discontinue
Hypothyroidism	N/A	Therapy with IMP can be continued while thyroid replacement therapy is instituted
Infusion Reaction	2^b^	Toxicity resolves to Grade 0–1
	3–4	Permanently discontinue
Pneumonitis	2	Toxicity resolves to Grade 0–1
	3–4	Permanently discontinue
Renal Failure or Nephritis	2	Toxicity resolves to Grade 0–1
	3–4	Permanently discontinue
All Other Drug-Related Toxicity^c^	3 or Severe	Toxicity resolves to Grade 0–1
	4	Permanently discontinue

Note: Permanently discontinue for any severe or Grade 3 drug-related AE that recurs or any life-threatening event

^a^ For participants who begin treatment with Grade 2 AST or ALT at Cycle 1 Day 1 of treatment, if AST or ALT increases by greater than or equal to 50% relative to baseline and lasts for at least 1 week then participants should be discontinued

^b^ If symptoms resolve within one hour of stopping IMP infusion, the infusion may be restarted at 50% of the original infusion rate (e.g., from 100 mL/hr. to 50 mL/hr). Otherwise dosing will be held until symptoms resolve and the participant should be pre-medicated for the next scheduled dose

^c^ Participants with intolerable or persistent Grade 2 drug-related AE may hold study medication at PI/delegate discretion

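### The Cycle 2 dosing window is Days 19 to 25 in the schedule but Days 18 to 24 in the rule that forces permanent discontinuation

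*Protocol article*

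**What the plan says.** **Dosing window.** Methods/design in the Protocol article states: "Nivolumab will be administered on Day 1 and Day 22 (± 3 days) for a total of two 21-day cycles". The Methods part of the Abstract gives the same schedule. The section on adverse events management and dose modifications then adds a rule on top of Tables 2 and 3. It permanently stops treatment for anyone whose second-cycle dose is missed "within the allowed window (Day 18 to Day 24) due to being unfit for dosing for any reason".

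**Day labels elsewhere.** Study procedures puts the pre-surgery visit and imaging at Day 43 and the post-surgery imaging at Day 127, and sets the second follow-up visit 126 days after the first dose. Statistical analysis labels that visit Day 127. Outcome measures and endpoints differs: "Secondary endpoints include ORR on pre-resection imaging at day 42". It also places the first PFS and OS assessment at day 126.

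**AST/ALT.** Table 1 admits participants with "ALT/AST levels ≤5× ULN". For those at Grade 2 on Cycle 1 Day 1, the dose-modification text says that discontinuation for AST or ALT deterioration "will be triggered only if ALT or AST increase by more than or equal to 50% compared to the measurement taken at initiation"; the rise must also persist for one week or more. The Table 3 row headed "AST, ALT, or Increased Bilirubin" holds treatment at Grade 2 until return to Grade 0 or 1, and discontinues permanently at Grade 3 or 4. The footnote for participants who start at Grade 2 is attached to the Grade 3–4 line only.

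**The concern.** Each rule reads clearly by itself, but together they give different answers for the same participant at the same dose. Ipilimumab is given on Day 1 only and nivolumab twice, so Cycle 2 is the only dosing occasion after Day 1. This is therefore the trial's only post-baseline dosing window, and missing it through unfitness is irreversible.

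At stake is whether an individual participant receives the second nivolumab dose. It also bears on how that participant is counted: as having completed or discontinued treatment, and possibly as in or out of the per-protocol set. Tolerability is part of the primary endpoint, so the discontinuation count should not depend on which section a site happened to read.

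**Working it through.** **1. The two windows**

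Inputs: Day 22 ± 3 days (Abstract and Methods/design); Days 18 to 24 (dose-modification section); 21-day cycles with the first dose on Day 1.

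- Start of Cycle 2: 1 + 21 = Day 22, which agrees with the schedule.
- Schedule window: 22 − 3 = 19 and 22 + 3 = 25, so Days 19 to 25.
- The discontinuation rule's Days 18 to 24 cannot be obtained from Day 22 ± 3. They follow from 21 ± 3: 21 − 3 = 18 and 21 + 3 = 24.
- Read as elapsed days after a Day 1 dose, 18 + 1 = 19 and 24 + 1 = 25, so the windows would coincide. The rule, however, is written in study days.

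| Study day | Schedule (22 ± 3) | Discontinuation rule (18–24) |
|---|---|---|
| 18 | too early | inside |
| 19–24 | inside | inside |
| 25 | inside | outside; permanent discontinuation if unfit until then |

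Two of the 8 days from Day 18 to Day 25 are classed differently.

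**2. The same slip elsewhere**

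With the first dose on Day 1, 42 elapsed days is Day 1 + 42 = 43, and 126 elapsed days is Day 1 + 126 = 127. Study procedures and Statistical analysis agree with this. In Outcome measures and endpoints, the imaging at day 42 and the PFS/OS assessment at day 126 are each one day short.

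**3. The AST/ALT rules**

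Take a participant who starts at Grade 2 and has a treatment-related rise of less than 50% that stays within Grade 2.

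- The stated AST/ALT trigger needs a rise of at least 50% for at least one week. It is not met, so this rule does not discontinue the participant.
- The Grade 2 line of Table 3 holds Cycle 2 until Grade 0 or 1. That is better than the participant's own starting value. The exception does not reach this line.
- If Grade 0 or 1 is not reached by Day 24, the window rule makes the discontinuation permanent.

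The outcome is a permanent stop after an AST/ALT rise below the threshold that the text names as the only trigger.

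**4. Size**

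The trial enrols up to 32 participants. One participant classed differently moves a proportion over 32 by 1/32 = 3.1 percentage points. The article does not say how many participants might first become fit on Day 25 or fall into the AST/ALT case, so the expected number cannot be calculated.

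**The case against.** The strongest reply is that this is a one-day slip in day origin with little effect on the analysis. Much of that stands. Elapsed-day counting explains the figures. The safety set takes everyone with at least one dose and the ITT set everyone enrolled, so neither depends on the window. The per-protocol set excludes only major violations, and nothing says that a one-day difference is major. But a likely cause does not remove the conflict: both texts are current, both use study days, and one carries an irreversible consequence. Condensing a protocol into an article can explain missing detail, but not two different windows for one dose.

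On AST/ALT, the reply is that Table 3 is a summary captioned for immune-related events, that a hold is not a discontinuation, and that the window rule is a separate, additional ground that applies whatever the reason for unfitness. This narrows the point. A reader might infer that every participant who starts at Grade 2, including one whose value never changes, is held and then lost. The documents do not support that. Other causes must be excluded before an event is called immune-related, and an unchanged pre-treatment value does not naturally qualify. The reply does not dispose of a treatment-related rise below 50% within Grade 2. The full protocol, which is not shown, may settle that case.

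A reader might also set the 50% rule against Table 3's note on life-threatening events. That note is general. The two can collide only if an AST or ALT rise is itself life-threatening and lasts less than a week, so this is not a broad conflict.

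**Conclusion.** The window contradiction is certain as written and small: one day at each end, with serious consequence only for a participant unfit through Day 24 and fit on Day 25. Day 18 is an inconsistency only. A dose given then would be early under the schedule, but it does not trigger discontinuation.

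The AST/ALT conflict is secondary and held with moderate confidence. It rests on reading the Grade 2 hold as applying to a treatment-related rise below 50% in a participant who started at Grade 2.

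Two further inferences should not be drawn. The Day 89 cut-off for surgical delay is not shown to be uncertain: it appears once, and no second figure competes with it. Nor do the visit 126 days after the first dose and the Day 127 label contradict each other; with the first dose on Day 1 they are the same date.

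No sample size, power or alpha depends on this point. The effect is on the treatment of individual participants and possibly on the per-protocol set. It should be corrected because the correction is easy and the consequence for a participant is irreversible, but it does not threaten the trial's conclusions.

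**What to change.** - Use one day-numbering convention, with the first dose as Day 1, and correct the day 42 imaging and day 126 PFS/OS labels in Outcome measures and endpoints to match the rest of the article.
- State the Cycle 2 dosing window once, and have the discontinuation rule refer to it.
- Reconcile the dose-modification text with Table 3: say whether the Grade 2 hold and the window rule apply to participants who start at Grade 2 AST or ALT, and put the same statement in both places.

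Which window and which AST/ALT rule are right is a clinical decision for the sponsor. The cost is a protocol clarification and a notice to sites; no design element or calculation has to be redone.

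### Table 3 gives opposite instructions for Grade 4 hypophysitis: the row allows restart or continuation, the Note requires permanent discontinuation (minor internal inconsistency)

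*Protocol article*

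**What the plan says.** All the text at issue is in the protocol article, under Adverse events management and dose modifications, in Table 3 and the lines below it.

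- **Note under Table 3:** "Permanently discontinue for any severe or Grade 3 drug-related AE that recurs or any life-threatening event". No toxicity is exempted.
- **Hypophysitis row:** Grades 2–4 share one line in the hold column. The restart column reads "Toxicity resolves to Grade 0–1. Therapy with IMP can be continued while endocrine replacement therapy is instituted".
- **Type 1 diabetes/hyperglycaemia row:** "Hold the IMP for new onset Type 1 diabetes mellitus or Grade 3–4 hyperglycemia associated with evidence of beta cell failure". Neither a restart criterion nor a discontinuation rule follows.
- **Hypothyroidism row:** the hold grade is marked not applicable, and the entry is "Therapy with IMP can be continued while thyroid replacement therapy is instituted".
- **Hyperthyroidism row:** "Hyperthyroidism 3 Toxicity resolves to Grade 0–1", and the next line orders permanent discontinuation at Grade 4.
- **AST/ALT/bilirubin row, Grades 3–4:** "Permanently discontinue (see exception below", with a footnote. This is the only row marked as carrying an exception to permanent discontinuation.

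Under Outcome measures and endpoints, safety and tolerability are assessed by "National Cancer Institute Common Terminology Criteria for Adverse Events (NCI CTCAE) v5.0 criteria".

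**The concern.** A site with a participant who has Grade 4 hypophysitis finds two instructions in one table. The row lets dosing resume or go on; the Note ends it. Nothing in the printed text says which takes precedence.

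The matter deserves attention because safety and tolerability is a primary endpoint, and the rule decides whether a participant is exposed to a further dose after a serious toxicity. It also bears on the analysis sets. The Statistical analysis section plans a per protocol analysis that leaves out participants with major protocol violations. Whether giving Cycle 2 after such an event departs from the protocol depends on which line is taken as the rule.

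**Working it through.** No arithmetic applies. The check sets each endocrine row, read at Grade 4, beside the Note.

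**Step 1: is Grade 4 the life-threatening level?** The article does not define the term, so this is an assumption. The table supports it in two ways. The Note and the last row of Table 3 both pair severe with Grade 3, which leaves life-threatening as the next level up. Seven of the ten toxicity rows also prescribe permanent discontinuation at Grade 4 (diarrhoea/colitis, AST/ALT/bilirubin, hyperthyroidism, infusion reaction, pneumonitis, renal failure/nephritis, and all other drug-related toxicity). The three that do not are hypophysitis, type 1 diabetes/hyperglycaemia and hypothyroidism.

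**Step 2: the four endocrine rows at Grade 4.**

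| Row | Row's instruction at Grade 4 | Against the Note |
|---|---|---|
| Hypophysitis | Hold; restart at Grade 0–1, or continue on replacement | Opposite |
| Type 1 diabetes/hyperglycaemia | Hold; nothing further stated | Unclear: restart is not permitted in terms, and discontinuation is not ordered |
| Hypothyroidism | Continue on replacement; Grade 4 not named and no upper limit given | Unclear: in conflict only by implication |
| Hyperthyroidism | Permanently discontinue | Agrees |

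Only the hypophysitis row names Grade 4 and also permits further dosing.

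**Step 3: is hypophysitis marked as an exception?** No. The AST/ALT/bilirubin row shows how the table marks one, and no endocrine row carries such a mark. Nor are endocrine toxicities exempt as a group, because Grade 4 hyperthyroidism leads to permanent discontinuation.

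**Step 4: how much dosing is at stake?** Under Methods/design, ipilimumab is given once, on Day 1, and nivolumab on Day 1 and Day 22. After Day 1, only the second nivolumab dose remains. The text before Table 3 permanently stops anyone who is unfit for that dose within Day 18 to Day 24. The two rules can therefore lead to different actions only when a Grade 4 event arises after the first dose and, by the end of that window, has either improved to Grade 0–1 or is being managed on replacement in a participant judged fit to be dosed. An event first arising after the second dose leaves no dose in dispute. The article gives no frequency for such events, so no expected count can be stated.

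**The case against.** The strongest reply is that the Note is an overlay on the rows. It already works that way for recurrence: Grade 3 diarrhoea/colitis may restart at Grade 0–1, yet a recurrent Grade 3 event means permanent discontinuation, and that is not a contradiction. On the same reading, the life-threatening clause simply overrides the hypophysitis row. This is a workable order of precedence, but the text does not state it. The reverse reading, that a specific row displaces a general note, is also open, and a site would have to choose.

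Other parts of the reply stand and limit the point:

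- Grade 4 is nowhere equated with life-threatening; that is inferred.
- A reader might see a second contradiction inside the hypophysitis row, between the hold column and "Therapy with IMP can be continued while endocrine replacement therapy is instituted". That sentence sits in the column on timing of restart and can be read in sequence: hold, restart at Grade 0–1, with hormone replacement no bar to dosing. It is loose wording rather than a clear conflict.
- A reader might infer that the reported primary results would shift. The documents do not support this. The discontinuation rate is not a named endpoint, the event is recorded under either rule, one dose is enough for the safety analysis set, and the step from Part 1 to Part 2 depends on surgical delays.
- Table 3 is presented as a summary, in an article that condenses a longer protocol. The full guidelines may settle the matter. The point rests on two printed statements that disagree, not on detail left out.

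**Conclusion.** The point holds in a narrow form, as a minor internal inconsistency. One of the ten toxicity rows, hypophysitis, conflicts with the Note at Grade 4, provided Grade 4 is taken as life-threatening. Two further rows leave the Note's application unclear.

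The table might tempt a reader to conclude that its endocrine rows as a group allow treatment after Grade 4 events. That goes too far: hyperthyroidism agrees with the Note, the type 1 diabetes/hyperglycaemia row gives no permission to restart, and hypothyroidism does not name Grade 4.

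At most one nivolumab dose per affected participant is in question, and the Cycle 2 window rule narrows the cases further. The inconsistency still merits correction, because a stopping rule in a trial with safety as a primary endpoint should not give two answers for the same participant. This review takes no view on which rule is right.

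**What to change.** The passages must be reconciled, and the sponsor's clinical team decides which rule stands.

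1. State whether the hypophysitis row or the Note governs at Grade 4. If the row is meant as an exception, mark it in the way the AST/ALT/bilirubin row is marked.
2. State how the Note applies to the type 1 diabetes/hyperglycaemia and hypothyroidism rows.
3. Say in the Note whether life-threatening means Grade 4.
4. Reword the hypophysitis entry so that hold, restart and continuation read as one sequence or as clearly separate cases.

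The cost is a wording correction to one table and its Note, with a clarification to sites if the full protocol carries the same text. It adds no procedures, participants or analyses.
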